## Abstract

**Background:**

The COVID-19 pandemic has a large impact worldwide and is known to particularly affect the older population. This paper outlines the protocol for external validation of prognostic models predicting mortality risk after presentation with COVID-19 in the older population. These prognostic models were originally developed in an adult population and will be validated in an older population (≥ 70 years of age) in three healthcare settings: the hospital setting, the primary care setting, and the nursing home setting.

**Methods:**

Based on a living systematic review of COVID-19 prediction models, we identified eight prognostic models predicting the risk of mortality in adults with a COVID-19 infection (five COVID-19 specific models: GAL-COVID-19 mortality, 4C Mortality Score, NEWS2 + model, Xie model, and Wang clinical model and three pre-existing prognostic scores: APACHE-II, CURB65, SOFA). These eight models will be validated in six different cohorts of the Dutch older population (three hospital cohorts, two primary care cohorts, and a nursing home cohort). All prognostic models will be validated in a hospital setting while the GAL-COVID-19 mortality model will be validated in hospital, primary care, and nursing home settings. The study will include individuals ≥ 70 years of age with a highly suspected or PCR-confirmed COVID-19 infection from March 2020 to December 2020 (and up to December 2021 in a sensitivity analysis). The predictive performance will be evaluated in terms of discrimination, calibration, and decision curves for each of the prognostic models in each cohort individually. For prognostic models with indications of miscalibration, an intercept update will be performed after which predictive performance will be re-evaluated.

**Discussion:**

Insight into the performance of existing prognostic models in one of the most vulnerable populations clarifies the extent to which tailoring of COVID-19 prognostic models is needed when models are applied to the older population. Such insight will be important for possible future waves of the COVID-19 pandemic or future pandemics.

**Supplementary Information:**

The online version contains supplementary material available at 10.1186/s41512-023-00144-2.

## Background

COVID-19 has a large impact worldwide, causing over 6 million deaths [1], various long-term health effects in a large group of individuals, and an increased burden on healthcare providers and medical institutions. Health outcomes of a COVID-19 infection can be severe, particularly in the older population [2]. In the Netherlands, it is estimated that disproportionately high mortality of 88.8% of all COVID-19 deaths occurred in the older population (≥ 70 years of age) even though they make up only 14% of the total population [3]. Similarly, these mortality proportions in older individuals were also relatively high in hospitalized (60%) and nursing home settings (40%) [3].

Hundreds of prognostic models have been developed to quantify (differences in) mortality risk or other outcomes in COVID-19 patients and to identify individuals at greater risk of developing various future health outcomes [4]. COVID-19 prognostic models have been used to facilitate informed shielding decisions by governments [5], identify higher-risk groups requiring ventilatory or critical care support early to enable targeted recruitment for randomized controlled trials [6], and deliver more personalized, risk-based treatments for which effectiveness is known to vary according to disease severity more precisely [7]. However, despite the development of hundreds of prognostic models, only a few models are of high quality and low risks of bias, according to a critical appraisal in a large living systematic review [4]. For those models that were appraised at a low risk of bias, information about their actual performance in external validation studies is scarce. Further, due to the added complexity of health conditions like frailty [8] and multimorbidity [9] in older individuals, we hypothesize that these prognostic models derived for the general adult population will underperform when validated in an older population.

In this protocol, we describe a comprehensive external validation study to evaluate the predictive performance of eight prognostic models in the older population, defined as individuals aged 70 and older, in hospital, primary care, and nursing home settings. The predictive performance of the prognostic models will be evaluated in a different population than they were derived on, being the older population of individuals aged 70 and older compared to the general adult population. One model will be evaluated in all healthcare settings (hospital care, primary care, and nursing home) to assess predictive performance across settings.

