#### Descriptive analysis

Participant characteristics and predictor information will be described in all study cohorts (overall and stratified on mortality outcome status) to identify differences in case-mix between the development and validation study populations [28]. These comparisons give insight into the expected model performance and transportability [26].

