#### Assessment of predictive performance

For each prognostic model, we will apply the model according to the authors’ original descriptions and evaluate its predictive performance. We will evaluate discrimination (the model’s ability to distinguish individuals who died after presentation with COVID-19 diagnosis from those who did not) and calibration (the agreement between predicted and observed mortality risks) in each cohort [32]. Discrimination will be assessed in all models by quantifying the area under the receiver operating characteristic curve, i.e., c-statistic [33], and pooled by taking the median c-statistic over imputed datasets and computing dispersion using the interquartile range [34].

Calibration will be assessed by visualizing the calibration of expected versus observed risk using LOESS-smoothed plots on stacked imputed data sets [35]. The GAL-COVID-19 mortality model, NEWS2 + model, Xie model, and Wang clinical model are model equations. For these models, calibration will be assessed in terms of the calibration-in-the-large coefficient and calibration slope [35]. The coefficients are again pooled on a log scale using Rubin’s rules in case of multiple imputed datasets [36]. For each performance measure, for each evaluated model, we will compute the point estimate, standard error, and 95% confidence interval.

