#### Decision curve analysis

Decision curve analyses will be performed to quantify the net benefit achieved by each model for predicting the originally intended endpoint across a range of risk thresholds ranging from zero to one [37].

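### The c-statistic has no case-mix benchmark, so a lower value in people aged 70 and over cannot by itself show that a model underperforms or needs tailoring

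*Protocol article*

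**What the plan says.** The Background of the protocol article states a directional hypothesis: "we hypothesize that these prognostic models derived for the general adult population will underperform when validated in an older population". It attaches no performance measure, comparator or threshold to it. The validation population differs from the derivation populations chiefly by age, "being the older population of individuals aged 70 and older compared to the general adult population". The discussion part of the abstract says that insight into performance "clarifies the extent to which tailoring of COVID-19 prognostic models is needed".

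The section Assessment of predictive performance plans the following:
- Discrimination: "Discrimination will be assessed in all models by quantifying the area under the receiver operating characteristic curve, i.e., c-statistic". No expected or case-mix-standardised value is named.
- Calibration plots: "Calibration will be assessed by visualizing the calibration of expected versus observed risk using LOESS-smoothed plots on stacked imputed data sets".
- Calibration coefficients, introduced after GAL-COVID-19, NEWS2+, Xie and Wang are named as model equations: "For these models, calibration will be assessed in terms of the calibration-in-the-large coefficient and calibration slope".

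The section Decision curve analysis adds net benefit for each model. The section Updating adds an intercept update for models that show miscalibration.

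Case-mix is handled in Descriptive analysis, where cohort characteristics are set against those of the development populations. The stated purpose is: "These comparisons give insight into the expected model performance and transportability".

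Table 1 lists age as a predictor for every model except SOFA.

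**The concern.** The c-statistic depends on two things: whether the predictor effects are right, and how widely the true risks are spread in the population studied. Removing everyone under 70 takes away much of the variation in age. For a model in which age carries weight, the spread of the linear predictor shrinks and c falls, even if every coefficient is correct for older people.

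The two explanations lead to different conclusions. If the predictor effects are wrong in older people, refitting or tailoring the model could help. If the age range is merely narrower, refitting the same predictors would gain nothing, because the model is already correct given those predictors. A descriptive table may suggest the direction in which c will move but not the distance, so it gives no value against which to read an observed c. A conclusion on tailoring that leaned on a low c could therefore be drawn for a model that is valid in this population.

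**Working it through.** **Plan's own scenario.** The protocol states no c-statistic. The only usable figure is the linear predictor assumed under Sample size, N(−3.9, 1). Integrating 1/(1+e^(−x)) over that distribution gives a mean risk of 3.1%, in line with the stated 3%.

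**Benchmark.** For a correct model with predicted risks p, the expected c-statistic is

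c_model = Σᵢ Σⱼ pᵢ(1 − pⱼ)·[1(pᵢ > pⱼ) + ½·1(pᵢ = pⱼ)] / [Σᵢ pᵢ · Σⱼ (1 − pⱼ)].

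Keeping the mean at −3.9 and changing only the SD of the linear predictor gives:

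| SD | c of a correct model |
|---|---|
| 0.5 | 0.638 |
| 0.75 | 0.700 |
| 1 (protocol) | 0.756 |
| 1.25 | 0.802 |
| 1.5 | 0.839 |

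Thus c = 0.70 is what a correct model would give at SD 0.75, and a sign of trouble at SD 1.25. An observed c cannot be read without the spread.

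**Effect of restricting age.** The inputs below are assumptions, not document figures:
- adult ages N(62, 17), truncated to 18–105;
- overall risk 20%;
- log-odds per year of age 0.03, 0.05 or 0.07;
- other predictors combined normal with SD 0.3 to 1.5, the same at all ages.

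Outcomes were generated from the model itself, so the model is correct by construction.

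| Log-odds per year | SD of other predictors | SD of LP, all → 70+ | c, all → 70+ | Fall |
|---|---|---|---|---|
| 0.03 | 0.3 | 0.57 → 0.38 | 0.654 → 0.606 | 0.048 |
| 0.03 | 0.5 | 0.70 → 0.55 | 0.683 → 0.649 | 0.034 |
| 0.03 | 1.0 | 1.11 → 1.03 | 0.765 → 0.747 | 0.018 |
| 0.03 | 1.5 | 1.58 → 1.52 | 0.830 → 0.820 | 0.010 |
| 0.05 | 0.3 | 0.87 → 0.50 | 0.721 → 0.636 | 0.085 |
| 0.05 | 0.5 | 0.96 → 0.64 | 0.737 → 0.669 | 0.068 |
| 0.05 | 1.0 | 1.29 → 1.08 | 0.793 → 0.755 | 0.038 |
| 0.05 | 1.5 | 1.71 → 1.55 | 0.845 → 0.822 | 0.023 |
| 0.07 | 0.3 | 1.18 → 0.64 | 0.777 → 0.668 | 0.109 |
| 0.07 | 0.5 | 1.25 → 0.75 | 0.787 → 0.694 | 0.093 |
| 0.07 | 1.0 | 1.52 → 1.14 | 0.824 → 0.766 | 0.058 |
| 0.07 | 1.5 | 1.89 → 1.60 | 0.862 → 0.826 | 0.036 |

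The fall runs from 0.010 to 0.109 and is largest where age dominates the linear predictor. A logistic recalibration fitted in the 70+ subset gave intercepts from −0.009 to 0.007 and slopes from 0.988 to 1.008. Calibration therefore identifies the model as valid while c falls.

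**Which models have that safeguard.** Setting Table 1 beside Assessment of predictive performance:
- GAL-COVID-19, NEWS2+, Xie and Wang contain age and get calibration-in-the-large and slope.
- 4C, APACHE-II and CURB-65 contain age and get LOESS plots and decision curves but no calibration coefficients. Raw c is their only planned numerical measure of discrimination or calibration.
- SOFA contains no age term, so the direct mechanism does not apply.

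The intercept update shifts every linear predictor by the same amount. It leaves the ranking, and so c, unchanged, and re-assessing c afterwards adds nothing on this question.

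**The case against.** A reader might infer that the hypothesis will be judged on raw c-statistics, or that it is close to confirmed by design. The protocol supports neither. No section ties underperformance to c or commits to comparing c with development values. Calibration is planned as well, and "Decision curve analyses will be performed to quantify the net benefit achieved by each model". The only action triggered by performance, the intercept update, depends on miscalibration. For the four equation models, the planned slope would show that a correct model is correct.

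Four further points can be made against the concern:
- *Case-mix is recognised.* This is true, and the comparison is explicitly linked to expected performance. It remains descriptive and yields no reference value.
- *Observed c is what matters to users aged 70 and over.* This stands as a description of how well a model ranks them. It does not settle whether tailoring is needed, which depends on why c is low.
- *The size rests on assumptions.* This stands. The simulations also hold the spread of the other predictors fixed, whereas the Background expects frailty and multimorbidity to add complexity in older people. A wider spread of those predictors could offset part of the fall, so restriction can lower c but need not do so in every cohort.
- *A benchmark may sit in an analysis plan that is not shown.* It may. The point here is narrower: the article fixes the hypothesis, the restricted population, the measure and the tailoring inference together, and that inference needs a reference value.

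**Conclusion.** The concern holds in limited form. The protocol names no case-mix benchmark for the c-statistic and no criterion for underperformance. A lower c in people aged 70 and over therefore cannot, on its own, show that a model is invalid there. In the assumed scenarios a correct model lost about 0.01 to 0.11. The gap is partly covered for the four equation models by their calibration coefficients. It is sharpest for 4C, APACHE-II and CURB-65.

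A second over-reading should be avoided: that any gap between observed and model-based c measures wrong predictor effects in older people. Other sources enter it. Table 1 gives the NEWS2+ outcome as ICU admission or death within 14 days, whereas the hospital cohorts use in-hospital mortality. The section Challenges and limitations expects predictor measurement to differ between cohorts. The gap is also subject to sampling error. With 754 people and 3% events, the approximate (Newcombe) standard error of c at 0.75 is 0.052, as large as many of the case-mix effects above.

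**What to change.** Add to Assessment of predictive performance, for every model that yields predicted risks:

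1. Report in each cohort the model-based c-statistic, computed from the predicted risks with the formula above, and the SD of the linear predictor (the logit of predicted risk for points-based scores). Compute both in each imputed dataset and summarise them as for the observed c.
2. Base statements that a model underperforms or needs tailoring on observed versus model-based c, with its uncertainty, together with calibration. Do not base them on observed c against development c.
3. State that any remaining gap may also reflect a mismatch in outcome definition, as with NEWS2+, and differences in predictor measurement.

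Predicted risks are needed anyway: decision curves over risk thresholds are planned for each model, and two scores were left out of the selection because they express risk only qualitatively. The cost is a few lines of code per model on data already in hand, slightly wider results tables and somewhat more cautious wording of the conclusions. No further data are needed.

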## Methods

We have adhered to the TRIPOD guidelines checklist for external validation studies [10] in reporting this study protocol (Supplementary file 4).

### Selection of COVID-19 prognostic models

In the living systematic review of diagnostic and prognostic prediction models for COVID-19 (www.covid-precise.org) [4], all published prediction models were reviewed using PROBAST (www.probast.org) [11, 12], a quality or risk of a bias assessment tool for prediction model studies. Using results from the fifth update of this review, we have identified all candidate prognostic models that predict the risk of mortality in individuals with COVID-19 infection with uncertain or low risk of bias. Fifteen candidate models met this criterion of which five prediction models (PRIEST [13], CUCAF-SF [14], CUCA-SF [14], and QCOVID [15] for males and females) were not included for validation due to the unavailability of data on certain predictors in the six cohorts of older patients while two prognostic scores (qSOFA [16] and NEWS [17]) were excluded because they express risk of mortality qualitatively rather than as a risk prediction (Supplementary file 1). Eight prognostic models were included for external validation (Fig. 1). Of these eight models, five were COVID-19-specific (GAL COVID-19 mortality model [18], 4C Mortality Score [19], NEWS2 + model [20], Xie model [21], and Wang clinical model [22]) and were developed in adult COVID-19 populations during the pandemic. Three prognostic models were already existing before COVID-19 pandemic and were used for the prediction of in-hospital mortality risk after admission for any respiratory infections or sepsis (APACHE-II [23], CURB65 [24], and SOFA [25]) (Table 1). The details of eight selected models can be found in Supplementary file 2.

**Fig. 1 Fig1:**
[figure not shown]
Flowchart for inclusion of prognostic models for external validation

**Table 1 Tab1:** Overview of selected prognostic models

Model name	Derivation country		Pre-existing or COVID-19 specific	Derivation health care setting	Derivation population	Intended moment of use	Predicted outcome	Predictors		Model type
**GAL-COVID-19-mortality model** [18]	Spain		COVID-19 specific model	Primary care	Adults (≥ 18 years) with confirmed COVID-19 diagnosis	First presentation with COVID-19 infection at general practitioner	Mortality (no prediction horizon reported)	• Age • Sex • Lymphoma/leukemia • Liver disease • Dementia • Ischemic heart disease • Chronic obstructive pulmonary disease • Diabetes mellitus • Chronic kidney disease		Prediction model
**4C-Mortality Score** [19]	UK		COVID-19 specific model	Hospital	Adults (≥ 18 years) with confirmed COVID-19 diagnosis	At hospital admission for COVID-19 infection	In-hospital mortality	• Age • Sex • Respiratory rate • Peripheral oxygen saturation on room air • Glasgow Coma Scale • Urea • C-reactive protein • Number of comorbidities (counted as chronic cardiac disease, chronic respiratory disease (excluding asthma), chronic renal disease, liver disease, dementia, chronic neurological conditions, connective tissue disease, diabetes mellitus, HIV or AIDS, malignancy, obesity)		Points-based score
**NEWS2 + model** [20]		UK	Pre-existing risk stratification score updated for COVID-19 patients	Hospital	Adults (≥ 18 years) admitted to the hospital with a confirmed COVID -19 diagnosis	• At hospital admission for non-nosocomial patients (i.e., community-acquired COVID infection) • At the date of symptom onset for nosocomial patients. If the date of onset was unavailable the date of positive SARS-CoV-2 RT-PCR minus 4 days was used instead	ICU admission or death within 14 days of admission	• Age • Peripheral oxygen saturation • Heart rate • Systolic blood pressure • Body temperature • Alertness • Supplemental oxygen flow rate • Urea • C-reactive protein • Estimated glomerular filtration rate • Neutrophil count • Neutrophil/lymphocyte ratio		Prediction model
**Xie model** [21]		China	COVID-19 specific model	Hospital	Adults (≥ 18 years) admitted to the hospital with a confirmed COVID -19 diagnosis	At hospital admission for COVID-19 infection	In-hospital mortality	• Age • Lactate dehydrogenase • Lymphocyte count • Oxygen saturation		Prediction model
**Wang clinical model** [22]		China	COVID-19 specific model	Hospital	Adults (≥ 18 years) admitted to the hospital with a confirmed COVID-19 diagnosis. Pregnant women were excluded	At hospital admission for COVID-19 infection	In-hospital mortality	• Age • History of hypertension • History of heart disease		Prediction model
**APACHE-II Score** [23]		USA	Pre-existing risk stratification score	Hospital	All newly admitted ICU patients	At admission to ICU	Mortality	• Age • Body temperature • Heart rate • Respiratory rate • Mean arterial pressure • Arterial oxygen tension • pH • Potassium • Sodium • Creatinine • Hematocrit • Leucocyte count • Glasgow Coma Scale • Chronic health evaluation		Points-based score
**CURB-65** [24]		UK, New Zealand, The Netherlands	Pre-existing risk stratification score	Hospital	Patients with community-acquired pneumonia	For triage at the emergency department	Mortality (30 days)		• Age • Alertness (new confusion) • Urea • Respiratory rate • Systolic blood pressure • Diastolic blood pressure	Points-based score
**SOFA Score** [25]		Unclear	Pre-existing risk stratification score	Hospital	All ICU patients	At admission to and during admission at ICU	ICU-mortality		• Arterial oxygen tension • Fraction of inspired oxygen ratio • Glasgow Coma Scale • Mean arterial pressure • Administration of vasopressors • Creatinine • Bilirubin • Platelet count	Points-based score

*COVID-19* Coronavirus disease of 2019, *ICU* Intensive care unit; *RT-PCR* Reverse transcription polymerase chain reaction, *SARS-CoV-2* Severe acute respiratory syndrome coronavirus

### Validation cohorts

Data for this external validation study is collected from six cohorts with older individuals presenting with COVID-19 infection in the Netherlands from three settings: a hospital setting (3 cohorts), primary care setting (2 cohorts), and nursing home setting (1 cohort) (Table 2).

**Table 2 Tab2:** Details of study cohorts

Healthcare settings	Name of cohort	Description	Models that are externally validated in the cohort
**Hospital setting**	CliniCo	6 Hospitals in the region of Nijmegen in the Netherlands	• GAL-COVID-19 mortality model • 4C Mortality Score • NEWS2 + model • Xie model • Wang clinical model • CURB-65 Score • SOFA Score
	COVID-OLD	15 Hospitals throughout the Netherlands	• GAL-COVID-19 mortality model • 4C Mortality Score • NEWS2 + model • Xie model • Wang clinical model • APACHE-II Score • CURB-65 Score • SOFA Score
	COVID-PREDICT	10 Hospitals throughout the Netherlands	• GAL-COVID-19 mortality model • 4C Mortality Score • NEWS2 + model • Xie model • Wang clinical model • CURB-65 Score • SOFA Score
**Primary care**	JHN/ANH/AHA	General practitioner centers in Utrecht and Amsterdam municipalities in the Netherlands	• GAL-COVID-19 mortality model
	PHARMO	General practitioner centers throughout the Netherlands	• GAL-COVID-19 mortality model
**Nursing homes**	Ysis	Nursing homes throughout the Netherlands	• GAL-COVID-19 mortality model

### Participants

The study participants consist of older individuals (≥ 70 years of age) presenting with highly suspected or reverse transcription polymerase chain reaction (RT-PCR) confirmed COVID-19 from March 2020 to December 2020 in hospital, primary care, and nursing home settings.

Before the widespread use of the RT-PCR test for COVID-19 diagnosis, participants were included using proxy criteria. In the hospital cohorts (CliniCo, COVID-OLD, COVID-PREDICT), the reported respiratory diseases that had COVID-like symptomology are used as an inclusion criterion until 31 March 2020. From April 2020 onwards, a confirmed RT-PCR test for COVID-19 is used as an inclusion criterion. In the primary care cohorts (PHARMO and JHN/ANH/AHA), the participants are included based on free text information and reports of respiratory infections. From June 2020 onwards, ICPC R83.03 for COVID-19 infection is used as an inclusion criterion. The nursing home cohort (Ysis) used RT-PCR as an inclusion criterion. Only participant data on the first presentation or admission of COVID-19 will be included. In the three hospital cohorts, admissions with a duration fewer than 7 days between discharge and readmission will be considered a single hospital admission.

